### Follow-Up

Twelve hours after the completion of the trial, a follow-up health checkup will be performed, and the participants will be asked if they are experiencing any physical discomfort. The trial work plan is summarized in Figure 2.

**Figure 2 F2:**
[figure not shown]
Trial work plan. The primary outcome measure will be MoCA. The remaining outcome measures will be for secondary outcomes.

### Data Management and Monitoring

Both paper files and electronic documents will be preserved for at least 5 years after publication. If readers have any questions, they can contact the corresponding author for access to the original data. Patient information will remain anonymous, including name, ID number, and telephone number. The protocol will be reviewed and revised by experts in acupuncture, emergency, methodology, and statistics. We will perform a pre-specified standard operating procedure, which includes screening patients, improving relevant inspection, acupuncture, filling out the CRF, assessing outcomes, and data management. Outcome assessments, completion of case report forms and data management will be closely supervised. We will be monitored by the IEC of the Third Affiliated Hospital of Henan University of Chinese Medicine, and it is independent from the investigators and sponsor which will audit trial conduct every 12 months. Any modifications and corrections to operation procedures will be fully documented using a breach report form, monitored, and submitted to the directors of the ethics committee and China Clinical Trial Registration.

### Data Analysis

We will use SPSS software version 21.0 (IBM Corp, Armonk, New York, US) to perform data analysis. Demographic and baseline data will be analyzed with standard descriptive statistics. Data will be presented as the mean ± standard deviation (SD). A repeated measure ANOVA is employed to analyze the electroacupuncture effects and the time effects on the behavioral data. The repeated measure ANOVA is also used for the analysis of ERP indices. ANOVAs are performed on the N2 and P3 components of the scalp electrodes in the Go/No-Go task. The accepted level of significance for all analyses will be *P* < 0.05.

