**Methods:**

We will recruit 60 healthy subjects. The participants will be randomly divided into a treatment group, a control group, a sham electroacupuncture group and a blank group, at a 1:1:1:1 ratio. The primary outcome will be determined by the change from baseline to 36 h in the MoCA score. The secondary results include the amplitude and latency of ERP N2 and P3, Go-hit rates, Go-RTs, No-Go-FA rates, the WCST, the Digit Span Subtest of the WAIS, the ESS score and FS-14. The 15 healthy subjects will not receive acupuncture treatment and ASD, but will receive EEG records and cognition functions test at the beginning and end of the experiment. Electroacupuncture intervention will be performed for 30 min once every 12 h, a total of three times. ERP measurements and other tests will be performed after baseline and ASD, and the statistician and outcome evaluator will be blinded to treatment allocation.

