### Sample Size

According to the pre-test study, the average MoCA scores in the treatment group, control group, and blank group are 26.70, 25.72, and 27.32, respectively, and the standard deviations are 1.03, 1.59, and 1.37, respectively. Using the sample size calculation method of multi-group mean, the sample size estimation [one-way analysis of variance (ANOVA)] *F*-test] method will use the test level α = 0.05 (bilateral) and test efficiency 1 – β = 0.90. The bilateral test will be used. The total sample size of 45 cases was estimated using PASS 15.0 software.

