## Discussion

The purpose of this trial is to assess the impact of acupuncture on the management of brain cognition control. It is obvious that cognitive function is impaired after sleep deprivation. We intend to compare the effects of time (baseline and 36-h ASD) and intervention (electroacupuncture, sham electroacupuncture and non-electroacupuncture treatment) on executive brain function using a visual Go/No-Go task with simultaneous EEG recordings. Acupuncture is a non-toxic, economical intervention with minimal adverse effects (32) that has been shown to be effective after the therapy (11).

There are several methodological limitations to this study: (1) Due to the characteristics of acupuncture is the non-blinding of the acupuncturist. (2) Only young male subjects will be included; so, the findings may not be generalizable to women and older people. (3) The sample size is small. Despite these limitations, we will use rigorous methodology in this study, and we hope that the trial will help provide new insights into the value of acupuncture and evidence of ERP in executive brain function.

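### The stated repeated-measures ANOVA names group and time effects but not the group-by-time term, and is not assigned to MoCA; baseline-adjusted ANCOVA would be clearer and more precise

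*Protocol article*

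**What the plan says.** The Data Analysis section gives one family of methods for outcomes. For behavioural data: "A repeated measure ANOVA is employed to analyze the electroacupuncture effects and the time effects on the behavioral data". For the electrophysiology: "The repeated measure ANOVA is also used for the analysis of ERP indices", followed by "ANOVAs are performed on the N2 and P3 components of the scalp electrodes in the Go/No-Go task". The Discussion describes the comparison in the same two-factor terms: "We intend to compare the effects of time (baseline and 36-h ASD) and intervention (electroacupuncture, sham electroacupuncture and non-electroacupuncture treatment"). Neither place mentions an interaction, a baseline covariate or a particular between-arm contrast.

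The primary outcome is defined in the Abstract: "The primary outcome will be determined by the change from baseline to 36 h in the MoCA score". Table 1 schedules MoCA, WCST, digit span, ESS, FS-14 and EEG once at baseline and once at 36 h. The Data Analysis section does not name MoCA. In the Secondary Outcomes section the behavioural variables are Go/No-Go reaction time, hit rate and false alarms, so the quoted sentence does not plainly reach MoCA. The one-way ANOVA in the Sample Size section serves only to size the trial.

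**The concern.** A group-by-time ANOVA yields three tests: group, time and their interaction. The text names the first two. Neither isolates what electroacupuncture does between baseline and 36 h. The group term averages a time point at which randomised arms are expected to be equal with the one at which they may differ. The time term averages over arms and compares none of them. The interaction is the term that matches the change endpoint, and it is the one not named.

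Two things are at stake. First, an analyst or reader who took the group term literally as the electroacupuncture effect would see a diluted estimate and a weak test. Second, even the correct term gives up precision that the scheduled baseline values would return. In a trial with 15 per arm, whose Discussion lists small sample size as a limitation, that precision is worth having.

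**Working it through.** **The plan's own figure.** Sample Size reports these pilot means: "the average MoCA scores in the treatment group, control group, and blank group are 26.70, 25.72, and 27.32, respectively". The matching SDs are 1.03, 1.59 and 1.37. The "method will use the test level α = 0.05 (bilateral) and test efficiency 1 – β = 0.90", with a total of 45. A noncentral F calculation with the pooled SD, √[(1.03² + 1.59² + 1.37²)/3] = 1.35, needs 19 per group, or 57 in all. At 15 per group the power is 81%. The 45 is therefore not reproduced at 90% power. That is a separate matter, and nothing below depends on it.

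**Inputs.**
- Electroacupuncture minus control: d = 26.70 − 25.72 = 0.98 (Sample Size).
- SD: σ = √[(1.03² + 1.59²)/2] = 1.34 (Sample Size).
- n = 15 per arm, from 60 participants at 1:1:1:1 (Abstract).
- Two measurements, baseline and 36 h (Table 1).
- Correlation r between them: not in the document. Assumed 0.3 to 0.8.
- Also assumed: the same SD at both times and in both arms, equal expected baselines under randomisation, and pilot means that describe 36 h scores.

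**What each term estimates, and its variance per subject.**
- Group main effect (mean of the two times): estimates (0 + d)/2 = 0.49; variance σ²(1+r)/2.
- Group-by-time, identical to the comparison of change scores: estimates d = 0.98; variance 2σ²(1−r).
- ANCOVA of the 36 h value on baseline and group: estimates d = 0.98; variance σ²(1−r²).

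ANCOVA relative to group-by-time: (1−r²)/[2(1−r)] = (1+r)/2.

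**Worked case, r = 0.5.** The standard error of an arm difference is √(variance × 2/15).
- Group main effect: √(0.75 × 1.34² × 2/15) = 0.42; ratio 0.49/0.42 = 1.16; power 20%.
- Group-by-time: √(1.00 × 1.34² × 2/15) = 0.49; ratio 0.98/0.49 = 2.00; power 49%.
- ANCOVA: √(0.75 × 1.34² × 2/15) = 0.42; ratio 0.98/0.42 = 2.31; power 61%.

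Powers come from the noncentral t, two-sided 5%, with 28 degrees of freedom (27 for ANCOVA). Over the range of r, with variances in units of σ²:

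| r | Variance: group / group-by-time / ANCOVA | ANCOVA ÷ group-by-time | Power: group / group-by-time / ANCOVA |
|---|---|---|---|
| 0.3 | 0.65 / 1.40 / 0.91 | 65% | 22% / 37% / 53% |
| 0.5 | 0.75 / 1.00 / 0.75 | 75% | 20% / 49% / 61% |
| 0.7 | 0.85 / 0.60 / 0.51 | 85% | 18% / 70% / 77% |
| 0.8 | 0.90 / 0.40 / 0.36 | 90% | 18% / 86% / 90% |

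**Check by simulation.** 20,000 trials at r = 0.5 gave mean estimates of 0.486 for the group term and 0.984 for group-by-time, against 0.49 and 0.98 expected.

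The ANCOVA variance is the large-sample one. It leaves out the small cost of chance baseline imbalance, so the gain at the highest r is slightly overstated.

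**The case against.** A reader might infer that the plan as written halves the treatment effect. The document does not support that. It lists the factors of the model and never says that the group main effect will be reported as the treatment estimate. The same model contains the group-by-time term, and the Abstract's change endpoint points to it. The 18% to 22% powers therefore describe a possible misreading, not the plan.

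A reader might also infer that the primary outcome has no planned analysis at all. That goes too far as well. This is a condensed article, and a statistical analysis plan may exist in which terms, covariates and contrasts are set out. What can be said is that the analysis paragraph, as published, does not reach MoCA.

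Three further objections stand in part.
- Change-score analysis and ANCOVA are both valid in a randomised trial, so ANCOVA is an improvement in precision and not the correction of an invalid method.
- The power figures use MoCA, whereas the quoted sentence concerns behavioural data, for which the document gives no effect size. The figures are illustrative. The one-half and the (1+r)/2 hold for any outcome with two measurements and equal SDs.
- Not every outcome fits a single-value ANCOVA. N2 and P3 have electrode and stimulus type as within-subject factors, which a repeated-measures model handles. For Go/No-Go, the task design section describes an evening baseline, a 0 h session and a 36 h session. If all three entered the model, the group term would be diluted to one third, not one half, and group-by-time would no longer be a single change score.

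A call for heteroscedasticity-robust standard errors because the pilot SDs range from 1.03 to 1.59 would be a preference. The sizes of the pilot groups are not given.

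**Conclusion.** The point holds as a wording fault together with an efficiency gain that needs no new data. The published analysis names two effects, neither of which isolates the treatment effect; it leaves unnamed the term that does, and it does not say which analysis applies to MoCA. Read as the treatment effect, the group term would give 0.49 in place of 0.98. Read correctly, through group-by-time, the analysis is unbiased, and ANCOVA would cut its variance by 35%, 25%, 15% and 10% at r of 0.3, 0.5, 0.7 and 0.8. In MoCA power that is 16, 12, 7 and 4 percentage points (53−37, 61−49, 77−70, 90−86). These sizes rest on an assumed r, a common SD, and pilot values for electroacupuncture against control. The document gives no pilot value for the sham arm.

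**What to change.** - **MoCA.** State that 36 h MoCA is analysed by ANCOVA with baseline MoCA as covariate and allocated group as factor, and report adjusted between-group differences with 95% confidence intervals.
- **Single-value secondary outcomes** (WCST, digit span, ESS, FS-14, and Go/No-Go reaction time, hit rate and false-alarm rate). Use the same form. For Go/No-Go, state which of the two sessions before deprivation is the baseline.
- **N2 and P3.** Keep the repeated-measures model with electrode and stimulus type as within-subject factors, and either state that group-by-time is the treatment effect or add the baseline value as a covariate.
- **Optional.** Robust standard errors.

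The cost is a change of wording. Table 1 already schedules the baseline measurements, so no visits, participants or tests are added.

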### Ethics and Dissemination

All candidates who agree to participate and who meet all of the inclusion criteria and none of the exclusion criteria will be provided an informed consent form to provide them with full understanding of what the study participation will entail and the potential risks. Participants have the right to discontinue participation at any time. Data will be used in the aggregate only, and no identifying characteristics of individuals will be published or presented. In the consent form, the participants will be asked if they agree to the use of their data, should they choose to withdraw from the trial. The participants will also be asked for permission for the research team to share relevant data with people from the regulatory authorities, where relevant. This trial does not involve collecting biological specimens for storage. The study conforms to the principles of the Declaration of Helsinki. Ethical approval has been obtained from the IEC of the Third Affiliated Hospital of Henan University of Chinese Medicine. The trial protocol has been registered at the Chinese Clinical Trial Registry. The results will be disseminated through journal articles, a master's thesis, or conference presentations.

## Discussion

The purpose of this trial is to assess the impact of acupuncture on the management of brain cognition control. It is obvious that cognitive function is impaired after sleep deprivation. We intend to compare the effects of time (baseline and 36-h ASD) and intervention (electroacupuncture, sham electroacupuncture and non-electroacupuncture treatment) on executive brain function using a visual Go/No-Go task with simultaneous EEG recordings. Acupuncture is a non-toxic, economical intervention with minimal adverse effects (32) that has been shown to be effective after the therapy (11).

There are several methodological limitations to this study: (1) Due to the characteristics of acupuncture is the non-blinding of the acupuncturist. (2) Only young male subjects will be included; so, the findings may not be generalizable to women and older people. (3) The sample size is small. Despite these limitations, we will use rigorous methodology in this study, and we hope that the trial will help provide new insights into the value of acupuncture and evidence of ERP in executive brain function.

## Trial Status

Recruiting will start in February 2022. The current protocol is version 1 of 27-12-2021. Patient recruitment is estimated to be completed around June 2022.

## Ethics Statement

The studies involving human participants were reviewed and approved by The Third Affiliated Hospital of Henan University of Traditional Chinese Medicine. The patients/participants provided their written informed consent to participate in this study.

## Abbreviations

ASD: acute sleep deprivation
ERPs: event-related potentials
EHQ: Edinburgh Handedness Questionnaire
SCL-90: Symptom Checklist-90
PSQI: Pittsburgh Sleep Quality Index
MoCA: Montreal Cognitive Assessment
WCST: Wisconsin Card Sorting Test
DS: Digit Span of the Wechsler Adult Intelligence Scale
WAIS: Wechsler Adult Intelligence Scale
ESS: Epworth Sleepiness Scale
FS-14: Fatigue Scale-14
ANOVA: analysis of variance
IEC: Institutional Ethics Committee
EEG: electroencephalogram.
